# Prone versus lateral position in acute hypoxemic respiratory failure patients with HFNO therapy: study protocol for a multicentre randomised controlled open-label trial

**DOI:** 10.1186/s13063-023-07761-8

**Published:** 2023-11-27

**Keywords:** Respiratory failure, High-flow nasal oxygen therapy, Prone position, Lateral position, Protocol

## Abstract

**Background:**

High-flow nasal oxygen (HFNO) therapy is a leading treatment technique for acute hypoxemic respiratory failure (AHRF), but its treatment failure rate remains high. The awake prone position (APP) has been proven to increase oxygenation and reduce the endotracheal intubation rate in patients with COVID-19-induced AHRF. However, the APP is poorly tolerated in patients, and its performance in improving prognoses is controversial. The lateral position has a similar mechanism and effect to the prone position, but it is more tolerable than the prone position. Therefore, it is worth exploring whether the lateral position is better for awake patients with AHRF.

**Methods:**

This is a protocol for a three-arm parallel-group multicentre randomised controlled open-label exploratory trial. A total of 583 patients from two hospitals in Chongqing, China, will be randomised to take the semi-recumbent position, lateral position, or prone position at a ratio of 1:1:1. Patients are all diagnosed with AHRF secondary to non-COVID-19 pneumonia or lung infection and receiving HFNO therapy. The primary outcome is ventilator-free days in 28 days. The secondary outcomes are the 28-day intubation rate, 28-day all-cause mortality, total position change time, the incidence of adverse events, number of hours using HFNO therapy, length of hospital and intensive care unit (ICU) stay, and others. We will conduct subgroup analyses on the arterial partial pressure of oxygen to the fraction of inspiration oxygen (PaO2/FiO2) ratio (> 200 mmHg or ≤ 200 mmHg), time from admission to intervention implementation (< 24 h or ≥ 24 h), position changing time, and different diagnoses.

**Discussion:**

This trial will explore the prognostic effects of the APP with that of the lateral position in awake patients with non-COVID-19AHRF and compare the differences between them. To provide evidence for clinical decision-making and further research on position management.

**Trial registration:**

This trial was registered in the Chinese Clinical Trial Registry. The registration number is ChiCTR2200055822. Registered on January 20, 2022.

**Supplementary Information:**

The online version contains supplementary material available at 10.1186/s13063-023-07761-8.

## Background

### Background and rationale

Acute hypoxemic respiratory failure (AHRF) is a group of diseases characterised by acute hypoxemia, increased respiratory drive, and respiratory failure, with a mortality of 40% [1–3]. It is the main cause of hospitalisation and mechanical ventilation in the intensive care unit (ICU) [4]. Helmet noninvasive ventilatory support and high-flow nasal oxygen (HFNO) are the most promising, first-line treatment techniques for mild-to-moderate hypoxemia associated with AHRF [5]. And HFNO is more widely used than helmet noninvasive ventilators [6] because it is well tolerated [7], can reduce lung injury [5], and has a lower treatment failure rate compared to standard oxygen therapy [8]. Despite the benefits mentioned above, HFNO’s failure rate is still as high as 48%, of which the intubation rate is 43%, and the 28-day mortality rate is 19% [6]. How to further decrease its treatment failure rate and increase prognoses in AHRF patients with HFNO therapy has become a more significant question for researchers.

The APP is usually considered the prone position applied to awake patients who have not received endotracheal intubation. It was reported to improve oxygenation and decrease endotracheal intubation rate with minimal costs and side effects [9, 10] in awake patients with AHRF secondary to COVID-19. Better effects were reported on patients whose arterial partial pressure of oxygen to the fraction of inspiration oxygen (PaO_2_/FiO_2_) ratio was < 300 mmHg with noninvasive respiratory support [11–15]. And longer duration is associated with better outcomes [3]. However, the APP is poorly tolerated in patients, and there is a lack of an effective method for improving patient tolerance. The mean tolerance time of most patients is less than 3.5 h [3, 16], which is far less than the recommended 12 h [17, 18]. So, detecting the time-effect relationship of the APP is difficult. So far, meta-analyses on APP have not found any other prognosis-related benefits of APP other than decreasing intubation rate [9, 10]. Whether it can improve patients’ prognoses is still controversial [19]. Patient-centred outcomes like ventilator-free days, hospital length of stay, and mortality are all meaningful outcomes. Moreover, ventilator-free days is an outcome that both doctors and patients care about, as using ventilators can be both expensive and cause some serious side effects [5, 20].

The lateral position was proved to have a similar mechanism [21] and effect as the prone position on patients receiving invasive mechanical ventilation [22], and it was easier to tolerate and implement [23, 24]. Researchers placed patients in the lateral position [24, 25] or alternated between the prone position and the lateral position [23, 26] and found that oxygenation was also improved in patients. And previous studies found that the 90° lateral position has the best ventilation effect compared to other angles [27]. However, we have not discovered any experimental study to compare the effects, especially the prognoses, of the lateral position with the prone position on awake AHRF patients [28]. Whether the lateral position is better for awake patients still needs further exploration.

In the preliminary trial, based on feedback from patients and medical staff, we summarized a set of methods to improve patient tolerance. As the COVID-19 pandemic is slowly getting under control, we intend to conduct an experimental study on non-COVID-19 AHRF patients and compare the prognostic effects of the lateral position with the prone position in terms of improved endurance time on them while undergoing HFNO therapy. And to determine whether these positions can help with prognoses and which position is more effective and practical for awake patients. The evidence will help clinicians make better decisions on position management for awake non-COVID-19 AHRF patients undergoing HFNO therapy and set the stage for further research on the effect of APP and that of the lateral position on the prognosis of AHRF caused by various factors.

### Objectives and hypothesis

The first objective of this study was to investigate the effects of prone and lateral positions on patients receiving HFNO therapy in terms of ventilator-free days in 28 days and other prognostic factors. The secondary objective is to compare the differences in the impact of the prone and lateral positions on the investigated factors.

The hypothesis of this study is that positioning AHRF patients in the prone position can lead to improved prognoses. Additionally, for awake patients, the lateral position might be more beneficial than the prone position due to its better tolerance.

## Methods

### Trial design

This is a three-arm, parallel-group, multicentre, randomised controlled, open-label exploratory trial. A total of 583 will be randomly assigned to be placed in the semi-recumbent position (control group), the prone position (experimental Group A), and the lateral position (experimental Group B) at a ratio of 1:1:1. The follow-up period was 28 days. We will conduct and report this trial according to Standard Protocol Items: Recommendation for Interventional Trials. The trial design flowchart is detailed in Fig. 1.

**Fig. 1 Fig1:**
[figure not shown]
Trial design flowchart. SRP, semi-recumbent position; PP, prone position; LP, lateral position; P/F, PaO_2_/FiO_2_

### Study setting

This trial will be conducted in the pulmonary and critical care medicine departments on three campuses of two tertiary A-level teaching hospitals in Chongqing, China, in general wards and the ICUs (The standards for admitting patients to the intensive care unit are shown in Additional file 1). If it is difficult to recruit patients, more departments and hospitals will be involved if they obtain their ethics committee approval.

### Sample size

We calculated the sample size with NCSS statistical software PASS 2021 (version number: 21.0.3). The estimation of ventilator-free days in 28 days for the control group was 19 days, with a standard deviation of 13, based on what was reported before [29] and the severity of the disease [30, 31]. After being placed in the prone position and lateral position, the ventilator-free days in 28 days are expected to increase to 23 days and 22 days, and a standard deviation of 12 and 11 respectively, according to the mean difference in recent researches [10, 29] and the potential benefits of the refined interventions [16, 32–35]. Using an analysis of variance model with a two-sided alpha level of 0.05 and a power of 0.8. The allocation ratio is 1:1:1, so 486 participants are needed. We estimated a dropout rate of 20% due to poor tolerance and our experience in the pilot trial, so a total of 583 patients will be enrolled.

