### Outcomes

#### Primary outcomes

The primary outcome variable is ventilator-free days in 28 days. It is defined as days free from invasive mechanical ventilation or noninvasive ventilation within 28 days after randomisation.

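### The planned prone-group SD of 12 cannot occur with a mean of 23 on a 0–28 day scale; if the planned means stand, the error is conservative, but the 486 and its power need restating

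*Protocol article*

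**What the plan says.** The protocol article names "ventilator-free days in 28 days" as its primary outcome (Primary outcomes) and adds: "It is defined as days free from invasive mechanical ventilation or noninvasive ventilation within 28 days after randomisation". Each patient's value is thus a count of days between 0 and 28.

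The Sample size section gives three planning pairs. For control: "The estimation of ventilator-free days in 28 days for the control group was 19 days, with a standard deviation of 13". For the other two arms, introduced in the order prone then lateral, the values "are expected to increase to 23 days and 22 days, and a standard deviation of 12 and 11 respectively". The pairs are therefore control 19 (SD 13), prone 23 (SD 12) and lateral 22 (SD 11). With an analysis of variance, alpha 0.05, power 0.8 and equal allocation, the section arrives at 486 patients, raised to 583 for dropout.

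**The concern.** On a bounded scale the mean and the SD are not free of each other. The nearer the mean lies to the upper end, the less room there is for spread. A mean of 23 out of 28 leaves only five days above it, and an SD of 12 is more than the scale can produce at that mean.

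The sample size is computed from these pairs. If one pair cannot exist, the stated N and power do not describe any possible trial, and a reader cannot tell from the text whether the mean or the SD should give way. The two corrections move the power in opposite directions, so the point needs an answer from the authors even if the number enrolled does not change.

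**Working it through.** **Inputs.** Scale 0–28 (Primary outcomes). Means 19, 23, 22; SDs 13, 12, 11; alpha 0.05; power 0.8; 486 patients, or 162 per arm (Sample size).

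**Step 1: reproduce the 486.** I used the one-way equal-variance ANOVA, with power from the noncentral F distribution.
- Grand mean: (19 + 23 + 22)/3 = 21.33.
- Sum of squared deviations of the means: (−2.33)² + 1.67² + 0.67² = 8.667.
- Average variance: (169 + 144 + 121)/3 = 144.67, a common SD of 12.03.
- Noncentrality at 162 per arm: 162 × 8.667/144.67 = 9.71. With a critical F of 3.014 on 2 and 483 degrees of freedom, power is 0.800.

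The smallest n per arm that reaches 0.8 is 162, so N = 486. Using the plain average of the SDs (12.0) also gives 486, with power 0.802. The plan's figure is reproduced, and the prone SD of 12 is one of the inputs behind it.

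**Step 2: the ceiling on the SD.** If X lies in 0–28, then X² ≤ 28X. So E(X²) ≤ 28m and Var(X) ≤ 28m − m² = m(28 − m).

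| Arm | Mean | Ceiling √(m(28 − m)) | Stated SD |
|---|---|---|---|
| Control | 19 | √(19 × 9) = 13.08 | 13, attainable |
| Prone | 23 | √(23 × 5) = 10.72 | 12, impossible |
| Lateral | 22 | √(22 × 6) = 11.49 | 11, attainable |

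Using the n − 1 divisor at n = 162 raises the prone ceiling only to 10.76. Swapping the two SDs does not help: 11 exceeds 10.72, and 12 exceeds 11.49.

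**Step 3: keep the means, correct the SD.** The means stay at 19/23/22 and the test is as in Step 1.

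| SDs (control/prone/lateral) | Average variance | Common SD | N for 0.8 | Power at 486 |
|---|---|---|---|---|
| 13/10.72/11 | (169 + 115 + 121)/3 = 135.00 | 11.62 | 456 | 0.829 |
| 13.08/10.72/11.49 (all ceilings) | (171 + 115 + 132)/3 = 139.33 | 11.80 | 468 | 0.816 |
| 13/10/11 (prone SD assumed) | (169 + 100 + 121)/3 = 130.00 | 11.40 | 438 | 0.843 |
| 13/9/11 (prone SD assumed) | (169 + 81 + 121)/3 = 123.67 | 11.12 | 417 | 0.862 |

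The second row is the worst case. No attainable set of SDs has a larger average variance at these means.

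**Step 4: keep the SD of 12, correct the mean.** An SD of 12 requires m(28 − m) ≥ 144, so m ≤ 14 + √(196 − 144) = 21.21. That is a gain of at most 2.2 days over control, against the planned 4. At means 19/21.21/22 with SDs 13/12/11, the sum of squared deviations is 4.837 and the noncentrality is 162 × 4.837/144.67 = 5.42. Power at 486 is then 0.535.

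**The case against.** The best reply is that nothing of consequence follows. For the planned means, Step 3 shows that 486 is enough under every SD the scale permits. The trial calls itself exploratory, and the number enrolled need not move. That stands, and it limits the point to a correction of a stated input.

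A reader might go further and infer that the trial is underpowered, setting 0.54 beside 0.83 as equally likely. The document does not support that.
- The Sample size section ties the expected gains to mean differences in recent studies and to the refined interventions. It gives no separate basis for the SD of 12, so the SD is the more natural figure to correct.
- The 0.54 sits on a boundary: an SD of 12 at a mean of 21.21 requires every prone patient to score exactly 0 or 28.
- It also puts prone below lateral (21.2 against 22), which reverses the planned order.

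A reader might also call the control and lateral SDs wrong. They are close to their ceilings, which implies that most patients lie near 0 or 28, but they are attainable. Whether they are realistic depends on the cited sources, which are not at hand.

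What the reply does not remove is the impossible pair itself. No reading of the sentence makes a mean of 23 and an SD of 12 compatible.

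**Conclusion.** The prone planning pair is impossible: SD 12 against a ceiling of 10.72. It is an operative input to the stated 486 and power 0.8. If the means 19/23/22 are kept, the error is conservative: at most 468 patients are needed and 486 gives at least 0.816. With only the prone SD lowered to its ceiling, the figures are 456 and 0.83. Power falls short of 0.8 only if the authors regard SD 12 as the firm figure.

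This rests on two things. The first is that the outcome lies in 0–28, which follows from its definition. The second is the equal-variance F test, which is the calculation that reproduces 486. An unequal-variance (Welch) calculation gives 534 on the stated inputs and 501 with the prone SD at 10.72. The direction is the same, but that is not the calculation behind the plan's figure. The prone SDs of 9 and 10 are assumptions that show the range.

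**What to change.** In the Sample size section, state which prone input is wrong and replace it with a mean and SD that satisfy SD ≤ √(m(28 − m)). Give the basis for the new figure. Rerun the ANOVA calculation and restate the required N and the power at 486. How the authors arrive at an attainable pair is their choice.

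The cost is one rerun and one corrected sentence. Enrolment can stay at 583, and no outcome, analysis or trial procedure changes.

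### The 20% dropout allowance multiplies 486 by 1.2 instead of dividing by 0.8, so 583 covers a loss of about 16.6% (a minor error, under 2 power points)

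*Protocol article*

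**What the plan says.** The Sample size section of the protocol article gives every input to the calculation. For the control arm: "The estimation of ventilator-free days in 28 days for the control group was 19 days, with a standard deviation of 13". For the prone and lateral arms, "the ventilator-free days in 28 days are expected to increase to 23 days and 22 days", with "a standard deviation of 12 and 11 respectively". The method is stated as "Using an analysis of variance model with a two-sided alpha level of 0.05 and a power of 0.8". The result is "The allocation ratio is 1:1:1, so 486 participants are needed".

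The section then makes the allowance for loss and fixes the enrolment total: "We estimated a dropout rate of 20% due to poor tolerance and our experience in the pilot trial, so a total of 583 patients". The formula for this step is not written out. The same total is carried into the Abstract and the Trial design section ("A total of 583 will be randomly assigned").

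Three other sections bear on what a dropout is:

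- Withdrawal criteria includes patients who refuse to change position partway through, or whose positioning time is below 1 h per day.
- Data collection and management says that the data drawn from the electronic record include those of withdrawn patients.
- Methods for additional analyses handles the missing values of withdrawn patients by intention to treat with multiple imputation.

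**The concern.** A dropout rate is a share of the patients enrolled. If 20% of those enrolled are lost, 80% remain, so the enrolled number must be the required number divided by 0.8. Multiplying the required number by 1.2 adds 20% of the smaller figure and falls short.

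The printed total agrees with the multiplication and not with the division. The required number, the dropout rate and the enrolment total therefore do not fit together, and the stated 80% power does not follow from the protocol's own figures. Nothing has been omitted through condensing: all three numbers are printed, and any reader can check them.

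**Working it through.** **Inputs** (all from Sample size): means 19, 23 and 22 days; SDs 13, 12 and 11; analysis of variance with three equal arms; alpha 0.05; power 0.80; dropout 20%; 486 required; 583 enrolled.

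**Step 1. Reproduce 486.**

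- Mean variance: (13² + 12² + 11²) / 3 = (169 + 144 + 121) / 3 = 144.67, so the common SD is 12.03.
- Grand mean: (19 + 23 + 22) / 3 = 21.33.
- Sum of squared deviations: (−2.33)² + 1.67² + 0.67² = 8.67.
- Noncentrality with n per arm: λ = n × 8.67 / 144.67.
- Power: probability that a noncentral F with 2 and 3n − 3 degrees of freedom and noncentrality λ exceeds the 5% critical value.

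| n per arm | Total | λ | Power |
|---|---|---|---|
| 161 | 483 | 9.65 | 0.798 |
| 162 | 486 | 9.71 | 0.8004 |

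So 486 is the smallest total with equal arms that reaches 80%. The plan's figure is confirmed, and it has no slack.

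**Step 2. Reproduce 583.**

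- By multiplication: 486 × 1.2 = 583.2, which rounds to the stated 583.
- By division: 486 / (1 − 0.20) = 607.5, so 608, or 609 for three arms of 203.
- Difference: 608 − 583 = 25 patients, and 25 / 608 = 4.1%. That is too large to be rounding.

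**Step 3. What 583 delivers.**

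- With a uniform 20% loss: 583 × 0.8 = 466.4, so about 466 remain, 20 fewer than 486.
- Largest loss that still leaves 486: 1 − 486 / 583 = 0.166, or 16.6%.

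**Step 4. Power, same formula.**

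| Patients analysed | Power |
|---|---|
| 466 (583 enrolled, uniform 20% loss) | 0.782 |
| 486 (the stated requirement) | 0.800 |
| 583 (no loss, effects as stated) | 0.871 |

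The cost of the slip is 0.800 − 0.782 = 0.018, or 1.8 percentage points.

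**Step 5. Sensitivity to where the loss falls.** The protocol does not split the 20% by arm. Suppose, as an assumption, that only the two positioned arms lose 20%. Each arm starts with 583 / 3 = 194.3. The control arm keeps 194.3 and the other two keep 194.3 × 0.8 = 155.5 each, about 505 in all. Power is then 0.839, above target.

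**The case against.** The strongest reply is that the shortfall may never occur. The protocol attributes the dropout partly to poor tolerance, and its withdrawal criteria cover patients who stop or hardly use the assigned position. Their ventilation data up to day 28 may still be in the record; the protocol plans to collect data on withdrawn patients and to analyse them by intention to treat with multiple imputation. The real loss of information could then lie below the 16.6% that 583 absorbs. If all 583 were analysed at the stated means, power would be about 87%. If tolerance loss fell only on the positioned arms, about 505 would remain, with about 84% power. The trial also calls itself exploratory.

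Much of this stands, and it limits the importance of the point. It does not repair the arithmetic: the Sample size section derives its total from a 20% allowance, and at that allowance the total does not return 486. Multiple imputation also does not restore the information in outcomes that are truly missing.

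A reader might go further the other way. Patients who stop positioning but stay in the analysis may dilute the effect, so one might infer that true power is far below 80%. The documents do not support a figure for this. They do not say what share of patients would gain nothing, they give no effect for partial positioning, and they do not say whether the expected 23 and 22 days already allow for imperfect adherence. If those values do, a further reduction would count non-adherence twice.

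**Conclusion.** The point holds as an arithmetic error of minor weight. On the protocol's own inputs, 583 is the product of the wrong operation: 608 (609 with equal arms) is the total that preserves 486 after a 20% loss. The consequence is about 78% power instead of 80%, or equivalently an allowance of about 16.6% instead of 20%.

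The 78% rests on three assumptions: that 20% are lost in every arm, that lost patients contribute no information, and that the stated means and SDs hold. The first two probably lean towards overstating the loss, given how the protocol treats withdrawn patients. A reader might infer that the trial is seriously underpowered or must enrol more patients. The figures do not support that: the loss is under 2 percentage points, and it vanishes if the missing outcomes stay at or below 16.6%.

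**What to change.** Keep 583 and correct the sentence in Sample size in one of two ways:

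- 583 enrolled patients allow for a loss of about 16.6% while keeping 486 and 80% power; or
- with a 20% loss, 583 enrolled patients leave about 466, which give about 78% power.

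In the same place, define the percentage as patients whose 28-day outcome is missing. State that patients who stop positioning but remain in the intention-to-treat analysis are not counted in it. This brings the allowance into line with Data collection and management and with Methods for additional analyses.

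The cost is one or two sentences and a slightly less favourable stated allowance or power. Enrolment, intervention and analysis stay as they are, and the total in the Abstract and Trial design need not change. Only if the sponsor wishes to keep both the 20% allowance and 80% power would the total have to rise to 608, or 609 for equal arms. An error of this size does not require that.

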### Recruitment

From June 2022 to March 2025, clinical staff will screen inpatients based on the eligibility criteria. If the patients meet the criteria, trained researchers will recheck and confirm their eligibility. Then inform the patients about the purpose and methods of the study, the risks and benefits of participating, their rights, and the safety and security measures taken during the trial through standardised communication that is easy to understand (Additional file 2). They will then obtain patients’ informed consent (Additional file 3). The patients will then be randomly assigned to three groups and instructed to take their assigned positions as soon as possible.

